## Data collection procedure

### Recall stage

The first experiment aims to test the hypothesis on the recall of information related to COVID-19 when it is presented by a prestigious role model. The entire experiment will be carried out online, through a platform specifically developed for research of this nature, by the Laboratory of Ecology and Evolution of Social-ecological Systems at the Federal University of Pernambuco.

The protocol, adapted from a study by Silva et al. [19], involves offering reading material to a participant, immediately followed by a distraction activity, and then conducting a surprise recall test of the information that was read (Fig 2).

**Fig 2 pone.0281991.g002:**
[figure not shown]
Recall experiment to be performed in Experiment I. Figure based on the protocol adapted from Silva et al. [18].

Upon clicking the research link, the participant will see a brief presentation of the research, followed by the consent and authorization forms to publish the data (referring to the TCLE). After accepting to participate, the volunteer will go to the next page, which will contain a form (S2 File) to fill out their data (gender, age, education, occupation, state where they live), region (urban or rural), education level, income, political inclination, and religion. The participants will then be directed to the next page, where there will be an alert, “*Now you will be asked to read a short text*. *Please read carefully as some questions will be asked later*.” after which the participant will be directed to one of the texts previously described. The texts will be randomized by the platform’s algorithm before being made available to each participant. After reading the text, they will be directed to a short attention test, which will verify whether the participant is paying attention to the experiment and also serve as a distraction activity. The test will consist of identifying certain figures (S3 File). Each page will have a two-minute time limit, which is an important step, as it ensures a standardized time for all the participants.

Finally, the volunteer will undergo a recall test, where they will be instructed to recount their respective reading text as accurately as possible. The instructions are as follows: “*Write down what you can remember about the text you read previously*. *Be as accurate as possible and don’t worry if you cannot remember all of the information*. *You have 10 minutes to complete this activity*.” At the end of the activity, a self-reporting stage of multiple-choice questions (S4 File) will follow with: [i] Who do you trust to seek information about COVID-19? (Participants can choose more than one option, and the alternatives will be health professionals, family members, friends, politicians, among other day-to-day personalities) [ii] What is your biggest source of information about COVID-19? (They can choose more than one option, and the alternatives range from online to physical media, such as newspapers and magazines) [iii] Have you been affected by COVID-19? (The options here will be yes or no, if yes, they will be asked to what extent they were affected) [iv] Has any member of your family been affected by COVID-19? (The options are the same as for the previous question) [v] Have you been vaccinated against COVID-19? The objective of this step is to perform data triangulation between the model that the person claims to follow and the factor that influenced the recall. Upon completion, the participant will see a message of acknowledgment and appreciation and will then be removed from the platform.

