## Abstract

In epidemic and pandemic contexts, such as that of COVID-19, epidemiological changes are continuous, and many people do not have access to accurate, up-to-date information. In this context, social learning can be an advantageous survival strategy. We investigate whether people remember and communicate information attributed to someone prestigious more often than that attributed to family members, politicians, and people with experience in public health. The experimental phase will include a recall stage and an information transmission stage, which will be based on a fictitious text containing an opinion about a drug treatment for COVID-19. There will be four versions of the text, and each participant will be assigned one of these versions for the investigation. The participants will be instructed to read the fictional story and then complete a distraction exercise. Subsequently, a recall test will be performed, where they will be asked to recount the story as accurately as possible. The second stage of the experiment is aimed at testing the transmission of information where we will conduct a linear chain transmission experiment, where eight chains of four participants will be used for each story. They will be asked to write down their recollection of the material. This text will undergo spelling error correction and then be sent to the next participant in the chain through the platform. At the end of the experiment, there will be a self-reporting questionnaire for the participants; this allows for triangulation of the data.

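### The trusted-source question comes after the randomised text, so setting it against recall is a post-exposure comparison and should be reported as exploratory

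*Protocol article*

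**What the plan says.** The order is set out under Data collection procedure, Recall stage. After consent, "the volunteer will go to the next page, which will contain a form (S2 File) to fill out their data". The listed items are demographic and social, ending with "region (urban or rural), education level, income, political inclination, and religion"; none asks about trusted sources. Next, "The texts will be randomized by the platform’s algorithm before being made available to each participant". The participant reads the text, does the attention task and writes out the recall. Then: "At the end of the activity, a self-reporting stage of multiple-choice questions (S4 File) will follow".

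Item [i] of that questionnaire asks "Who do you trust to seek information about COVID-19". More than one answer is allowed, and "the alternatives will be health professionals, family members, friends, politicians, among other day-to-day personalities". Item [ii] asks about the main information channel, from online to print media. Items [iii] to [v] cover COVID-19 history and vaccination. The purpose of the step is to "perform data triangulation between the model that the person claims to follow and the factor that influenced the recall". The Abstract repeats the idea: "At the end of the experiment, there will be a self-reporting questionnaire for the participants; this allows for triangulation of the data".

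In the Transmission stage the self-report comes later still, after the recall and a second written task. Under Data analysis, Hypotheses 1 and 2 are tested with type of role model as the only fixed effect and participant as a random effect. The self-report is not in that model.

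**The concern.** Triangulation is informative when the second source of evidence is independent of the first. Here the answer about trust is given minutes after the participant has read, and rewritten, a favourable opinion voiced by one kind of source. Physicians, politicians and family members are randomised conditions, and health professionals, politicians and family members are answer options. Table 1 also describes the prestigious source as one the reader already follows and looks up to, which is close to what item [i] is meant to capture.

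Two routes can then create agreement between stated trust and recall. The text may itself raise endorsement of its source. And a reader who engages more closely may both recall more propositions and be readier to tick the source just read about. Because several answers are allowed, a tick can be added without displacing another. At stake is the supporting statement that recall lined up with the model a person follows.

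**Working it through.** **Sequence.** Background form (no trust item), randomised text, attention task, written recall, (transmission stage only: second written task), item [i]. Nothing listed measures trust before exposure. Item [i] is therefore post-exposure in both stages.

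**Plan figure.** The article gives no figure on this point. The only plan number used below is the recall-stage sample of 327. It reproduces: one standard-normal covariate, odds ratio 1.81, base probability 0.1, R² = 0, one-sided α 0.05 and power 0.95, by the variance-corrected Demidenko method, give 326.2, rounded up to 327.

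**Illustration 1 (all rates assumed).** Half the readers are attentive: they recall 70% of propositions and 30% tick the source just read. Half are not: 40% and 10%. Prior trust has no effect.

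- Tickers: 0.5 × 0.30 + 0.5 × 0.10 = 0.20. Attentive share 0.15 / 0.20 = 0.75. Recall 0.75 × 0.70 + 0.25 × 0.40 = 0.625.
- Non-tickers: 0.35 + 0.45 = 0.80. Attentive share 0.35 / 0.80 = 0.4375. Recall 0.4375 × 0.70 + 0.5625 × 0.40 = 0.531.
- Gap: 0.625 − 0.531 = 0.094, about 9 points, with no preference behind it.
- If both groups ticked at the same rate, the attentive share would be 0.50 among tickers and non-tickers alike, both would recall 0.55, and the gap would be zero.

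**Illustration 2 (simulation, all rates assumed).** There are 327 participants and 2,000 runs. Engagement e is standard normal. Recall is the number of 7 propositions remembered, each with log-odds 0.8e. Before reading, 40% trust the assigned source, independently of recall. Exposure turns a non-truster into an endorser with probability (d / 0.6) × 2Φ(e), which averages to a rise of d in the whole sample. A two-sided 5% t-test compares recall between endorsers and others.

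| Rise d in endorsement | Rejects, trust asked before | Rejects, trust asked after | Mean false gap after (of 7) |
|---|---|---|---|
| 0 points | 5% | 5% | 0.00 |
| 5 points | 5% | 11% | 0.14 |
| 10 points | 5% | 30% | 0.28 |
| 15 points | 5% | 60% | 0.43 |

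**Would a comparison across texts reveal such a shift?** Compare endorsement of a given source in the quarter of participants who read its text (327 / 4, about 82) with the other three quarters, two-sided 5%. For an underlying endorsement of 20% to 60%, power is 12–17% for a 5-point shift, 35–47% for 10, 66–77% for 15 and 89–94% for 20. A table by text is worth having, but the absence of a significant difference would not show that the answer is free of exposure.

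**The case against.** The strongest reply is that nothing confirmatory rests on item [i]. The test of Hypotheses 1 and 2 compares randomised texts, and the self-report enters no model. That stands. A reader might infer that the main hypothesis tests are biased; the Data analysis section does not support that.

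Second, the article speaks of the model a person claims to follow. It does not call the answer a baseline preference, and it announces no comparison of trust between texts. That also stands. The point is about what the answer can support, and no misuse is shown. How the triangulation will be carried out may be in a fuller plan.

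Third, a reader might infer that the item simply belongs in the background form, at no cost because every arm would see it. Being asked equally does not mean being affected equally. Someone who has just ticked health professionals and left politicians blank may read a physician text and a politician text differently, which would act on the randomised contrast itself. Asking at the end protects the main experiment, so the order is a trade-off.

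Fourth, the exposure is narrower than it first looks. Item [ii] lists media channels, so it is little exposed. The article does not name digital influencers among the options of item [i], and the S4 File is not shown. In generations 2 to 4 of a chain, participants read a predecessor's recall, from which the source may have dropped out. Participants who do not complete the attention task are excluded, so a half-inattentive sample may be too pessimistic.

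Finally, stated trust in real-life sources may barely move after one short text about an unnamed source. The documents cannot settle this, and with no shift there is no distortion.

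**Conclusion.** The point holds in a limited form. Item [i] is a post-exposure answer whose options overlap the randomised role models, so its agreement with recall could have been produced by the text or by the reader's engagement. It cannot by itself show whom the person followed beforehand. The order and the intended use are both stated in the article, so this does not depend on detail left to another document.

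The size is unknown. The false gap of about 9 points, and the rejection rates of about 11% to 60% for shifts of 5 to 15 points, rest entirely on assumed figures and show the mechanism only. The damage is confined to a supporting conclusion. Hypotheses 1 and 2, the sample size and item [ii] are essentially untouched. The judgement relies on the questionnaire items as listed in the article, since the S2 and S4 Files are not shown.

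**What to change.** Keep item [i] at the end and change how it is used:

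- Tabulate the answers across the four randomised texts in the recall stage, and by condition and generation in the transmission stage.
- Report the triangulation as exploratory and post-exposure.
- Do not interpret the answer as whom the person followed before reading, particularly if it differs by text. Do not take a non-significant difference as clearance, given the power shown above.

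The cost is one extra table and a weaker supporting claim; the experiment itself does not change.

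Moving item [i] to the background form, placed among other items, is an option for the sponsor to weigh. It would give a pre-exposure answer, at the risk of priming readers differently by arm. That choice has to be made before data collection, because a pre-exposure answer cannot be recovered later.

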### Transmission stage

The second experiment to be carried out aims to test the hypothesis referring to the transmission of information related to COVID-19: specifically, on whether the presence of a prestigious role model favors the transmission of information over successive generations. Similar to the first experiment, this one will be carried out online, through a platform specifically developed for research of this nature, by the Laboratory of Ecology and Evolution of Socioecological Systems at the Federal University of Pernambuco.

A linear transmission chain experiment will be carried out, a method originally developed by Bartlett [29], which has been used in studies of cultural evolution over the years. It allows for the simulation of information transmission along a chain of individuals and occurs as follows: the first participant in the chain reads the material and, after a distraction task, is asked to recall the material read. In the original method, the resulting recall is then passed to the second participant, who does the same, and this continues along the chain (Fig 3). We will test 16 chains of four participants (representing four generations) for each proposed condition, totaling 64 chains.

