### Project

We intend to investigate whether people remember and transmit information more often when attributed to a prestigious source, in a pandemic scenario. We will use an online platform to carry out an experimental study, without the need for follow-up. The experiment will be conducted in two distinct stages, a recall stage as well as a stage for transmitting the information, both of which will be based on a fictitious text offered to the participants. This text will contain information about the use of a drug for COVID-19. There will be four versions of the text, one for each role model to be tested. Each version will consist of the same information, but only the role model attributed to the information being transmitted will change.

Since the experiment will be carried out online, there will be no need for blinding, on the part of the researchers, in carrying out the experiment and analyzing the results. More information is provided below about the selection of information along with a detailed procedure of the experiments. All data from the survey will included as supplementary material in the final articles.

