### Sample size

Individuals aged 18 years and older with access to the Internet will be selected to participate in the research. The recruitment of volunteers will be carried out through the dissemination of the survey on social networks such as Instagram, Twitter, Facebook, WhatsApp, and E-mail. To determine the sample size for the recall stage, we used the G*Power 3.1.9.7 software [25]. We conducted an *a priori* analysis to determine both the sample size and its power. As a basis for the study, we took the effect size (Odds ratio = 1.81) in a study by Bonin et al. [26] as it is the most recent study that brings memory-related variables and employs the same statistical test that we propose to use. We calculated a sample size of 327 people with an explanatory power of 95% and z = 1.64. The default for Pr(y = 1|x = 1)H0 in the G*Power software is 0.2 (i.e., a 20% probability of the event occurring if the null hypothesis is true). However, we use 0.1 to obtain an even more reliable sample size for the phenomenon we are investigating. We consider an α of 0.05, a Power (1-β err prob) of 0.95, R^2^; = 0, and normal distribution. Fig 1 presents the parameters used for this calculation.

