**Fig 1 pone.0281991.g001:**
[figure not shown]
Parameters used to calculate the sample size based on a power analysis.

The calculation for the transmission stage was based on the same parameters. However, as this stage will be conducted in transmission chains of four people each, we divided the total number of 327 people by 4 and rounded the result to the nearest whole number, arriving at a total of 21 chains per text used and 336 participants (an increase of 9 people from the calculated sample).

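### The transmission stage has three conflicting sizes (8, 16 and 21 chains per text), and only 21 reaches the calculated sample of 327

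*Protocol article*

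**What the plan says.** All references are to the Protocol article.

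- **Abstract:** "eight chains of four participants will be used for each story".
- **Sample size, paragraph after Fig 1:** the transmission stage starts from the recall-stage calculation ("The calculation for the transmission stage was based on the same parameters") and is converted into chains of four, "arriving at a total of 21 chains per text used and 336 participants (an increase of 9 people from the calculated sample".
- **Transmission stage, under Data collection procedure:** "We will test 16 chains of four participants (representing four generations) for each proposed condition, totaling 64 chains".
- **Project:** "There will be four versions of the text, one for each role model to be tested". There are therefore four conditions, and story, text and condition refer to the same unit.

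The recall-stage calculation that is carried over is in the Sample size section: "We calculated a sample size of 327 people with an explanatory power of 95% and z = 1.64". Its other inputs are an odds ratio of 1.81, a null event probability lowered from the software default of 0.2 ("we use 0.1 to obtain an even more reliable sample size"), alpha 0.05, R² = 0 and a normal predictor.

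**The concern.** The three statements describe one experiment, and each stands in an intact sentence of the current text. None is presented as a pilot, a subset or a superseded version. Two of them are complete designs that agree internally: 16 chains in four conditions is 64 chains, and 21 chains of four in four texts is 336 people. The Abstract supplies a third. The fault is therefore an inconsistency between sections. No section has its own arithmetic wrong.

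Two things are at stake. First, the stated calculation supports only one of the three sizes, yet the section that describes how the experiment will be run gives a different one. Second, with conflicting targets a reader cannot tell when recruitment for the test of Hypothesis 1 is complete. Stopping at 32, 64 or 84 chains could each later be presented as following the published protocol.

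**Working it through.** **1. Chains and people.** Four people per chain and four texts, so people = chains per text × 4 × 4.

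| Source | Chains per text | Chains in all | People | Against 327 | Against 336 |
|---|---|---|---|---|---|
| Abstract | 8 | 32 (derived) | 128 (derived) | −199 | −208 |
| Transmission stage | 16 | 64 (printed) | 256 (derived) | −71 | −80 |
| Sample size | 21 | 84 (derived) | 336 (printed) | +9 | 0 |

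The Sample size section treats 327 as the calculated sample and 336 as that number rounded up to whole chains. Shortfalls from the calculation are therefore 71 and 199; 80 and 208 are shortfalls from the rounded target.

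The rounding can be followed: 327/4 = 81.75, or 82 chains; 82/4 = 20.5, or 21 chains per text; 21 × 16 = 336 = 327 + 9.

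**2. Reproducing the plan's 327.** Inputs from the Sample size section: OR = 1.81, p0 = 0.1, power 0.95, R² = 0, standard normal predictor. The critical z of 1.64 implies a one-sided 0.05 test. The formula is the variance-corrected Wald formula for logistic regression:

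n = (z_α·√v0 + z_β·√v1)² / (ln OR)²

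- ln 1.81 = 0.5933, squared 0.3520.
- z_α = z_β = 1.645.
- The marginal event probability, averaging over the predictor, is 0.1125. Hence v0 = 1/(0.1125 × 0.8875) = 10.016, √v0 = 3.165.
- The variance term v1 under the alternative, by numerical integration of the information matrix, is 11.221, √v1 = 3.350.
- n = (1.645 × 3.165 + 1.645 × 3.350)² / 0.3520 = 326.2, rounded up to **327**, as stated.

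Other one-sided formulas with the same inputs give 342 (Hsieh) and 345 (no variance correction). Two-sided versions give 390 to 415. The variance-corrected one-sided form is the one that returns the plan's number.

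**3. The same formula at the three sizes.** Power = Φ[(√n·ln OR − z_α·√v0)/√v1], with z_α·√v0 = 5.206.

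- n = 336: (10.876 − 5.206)/3.350 = 1.693, power 95.5%.
- n = 327: (10.729 − 5.206)/3.350 = 1.649, power 95.0%.
- n = 256: (9.493 − 5.206)/3.350 = 1.280, power 90.0%.
- n = 128: (6.713 − 5.206)/3.350 = 0.450, power 67.4%.

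Across the one-sided variants in step 2 the figure is 88.3% to 90.0% at 256 and 64.0% to 67.4% at 128.

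**4. What these figures are.** The formula takes one binary outcome per person, a normally distributed predictor and independent people. The Data analysis section plans seven propositions per participant, a participant random effect and a four-level factor, and the data come from chains. The power percentages therefore describe the plan's calculation. They do not describe the planned analysis.

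**The case against.** The strongest reply accepts that the numbers differ but disputes how much follows from it.

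- **The power of the smaller designs is unknown.** A reader might infer that 64 or 32 chains cannot give 95% power. The document does not support that. Seven outcomes per person add information, while dependence within persons and within chains removes it. No variance component or intraclass correlation is given, so the true power of 32, 64 or 84 chains cannot be derived. For the same reason, 336 cannot be said to deliver 95%. What stands is narrower: the stated calculation supports only 21 chains per text.
- **A target does exist.** A reader might infer that recruitment has no defined end. That goes too far, since the Sample size section derives one number and explains it. The problem is conflicting targets.
- **Result-dependent stopping is not described.** A reader might infer that stopping on a favourable result is planned or likely. No section mentions interim looks or such stopping. It stands only as a possibility that the conflicting text fails to rule out.
- **The abstract is a summary.** Staff are unlikely to run the experiment from it. The working conflict is 16 against 21, which under the plan's formula moves power from about 95% to about 90%; the fall to 67% arises only from the Abstract. This is fair and limits the practical size of the point, but does not remove the need for one stated size.

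The allowance for a condensed article does not help here, because this is a contradiction between printed numbers and not an omission.

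**Conclusion.** The point holds and must be fixed before the transmission stage is run or reported. The plan states 8, 16 and 21 chains per text for the same experiment, and only 21 reaches the calculated 327. The size in the procedure section is 71 people below that number and the size in the Abstract 199 below. On the plan's own inputs the type II error rises from about 4.5% at 336 to about 10% at 256 and about 33% at 128.

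The counts rest only on four texts and four people per chain, both of which the document states. The power figures also rest on the plan's simplified formula and on reading z = 1.64 as a one-sided test. They show which size the calculation supports, and no more than that.

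**What to change.** Reconcile the Abstract, the Sample size section and the Transmission stage section to one size, stated as chains per text, total chains and total participants.

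- **If the calculated size was intended:** change the Abstract and the Transmission stage section to 21 chains per text, 84 chains and 336 people.
- **If 16 per condition is the operating plan:** change the Abstract and the Sample size section to 16 chains per text, 64 chains and 256 people, and restate power as about 90% under the plan's formula.

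In either case, say that the power figure treats participants as independent with one outcome each.

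The cost is wording only if 21 was already intended, and wording plus a less favourable power figure if 16 is kept. If 16 was the operating plan and the team moves to 21, that means 84 − 64 = 20 more chains and 80 more volunteers. In that case restating the power is the cheaper route.
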